## Introduction

Migraine is a recurrent, severe and primary headache disorder, manifesting unilaterally, throbbing in nature, and lasting 4 to 72 hours [1]. Migraine presented with a global age-standardised prevalence of 14.4% and was ranked as the second most disabling disease in 2016, with an estimated years of life lived with disability (YLDs) of 45.1 million [2]. In China, the number of migraineurs was estimated to be 132 million, with six million YLDs, in 2017 [2, 3].

According to the International Classification of Headache Disorders, 3^rd^ edition (ICHD-3) [1], migraine is typically divided into migraine with aura and migraine without aura. Migraine can also be categorised as episodic or chronic, according to its frequency. However, episodic migraine can progress to chronic migraine at an annual rate of 2.5% [4].

Migraine patients are more likely to suffer from psychiatric disorders including depression and general anxiety disorder [5, 6], as well as sleeping disorders such as insomnia [7]. These comorbidities are more commonly seen in chronic migraine compared with episodic migraine [8], and also in migraine with aura compared with migraine without aura [9, 10]. Furthermore, the comorbidities in episodic migraine indicate a poor prognosis, leading to poorer quality of life and limiting the response to treatments [7, 11], and also increase the risk of progression to chronic migraine and medication-overuse headache [1, 12, 13].

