Migraine is usually managed with medications for relieving symptoms in the acute stage, and with prophylactic treatment for reducing the frequency and severity of future attacks. The acute medications include aspirin, nonsteroidal anti-inflammatory drugs, paracetamol, antiemetics, steroids, and triptans. Prophylactic pharmacotherapies include calcium channel blockers, beta-blockers, tricyclic antidepressants, candesartan, pizotifen, angiotensin-converting enzyme inhibitors, selective serotonin reuptake inhibitors (SSRI), serotonin norepinephrine reuptake inhibitors (SNRI), antiepileptics, Botulinum toxin A and calcitonin gene-related peptide (CGRP) [14, 15]. Among them, only tricyclic antidepressants, SSNI and SNRI can be adopted for migraine comorbid with depression [14–16]; Botulinum toxin A is suggested for chronic migraine. Medical devices for migraine include occipital nerve block, vagus nerve stimulation, transcutaneous supraorbital nerve stimulation and transcranial magnetic stimulation [14–16]. However, approximately 30–40% of migraineurs are dissatisfied with current treatments, especially those suffering from chronic migraine [17, 18] and migraine with comorbidities [19–23], citing insufficient treatment effects, low tolerability, and unbearable side effects [24].

Acknowledging the above-mentioned limitations, there is an urgent need to identify alternative or complementary therapies to assist current conventional managements. Chinese herbal medicine (CHM), which is often prescribed to migraine patients in China [25], has gained clinical research evidence as an effective alternative or complementary therapy for migraine in recent years. However, most of the existing evidence has been generated from randomised controlled trials (RCTs) [26–30] and RCT-based systematic reviews [31–34]. Under controlled settings, RCTs usually apply strict selection criteria and provide unified treatments to all participants [35]. Such design may not reflect the complexity of migraine and its comorbidities [36], nor reflect the real-world practice of CHM which is commonly tailored according to individual’s syndrome differentiation [37]. Hence, the research evidence obtained from previous explanatory RCTs and systematic reviews need to be supplemented with more real-world evidence.

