#### Data collection

The study will employ a structured CRF (S1 File), which has been specifically designed for this study, including demographic information, symptoms, treatment details, relevant validated questionnaires, participants’ feedback and adverse events (AEs). Face-to-face data collection will be conducted at baseline, while evaluations at other timepoints can be completed using online CRFs or hard copy CRFs, according to participants’ preference. Online data collection will be conducted via the online survey service provider Wenjuan.com (www.wenjuan.com). Participants will be required to take migraine diary and record details of each migraine attack (S2 File). Data of patient-reported MBS, treatments, examinations and diagnostic information will also be extracted from the clinical records by the researcher.

The data to be collected from CRF is outlined below:

*Demographic and general information*. Demographic information including age, gender, general information such as family history, migraine subtypes and other medical histories will be collected upon participant enrolment.

*Patients’ preferences and concerns*. Patients’ preference and concerns regarding CHM treatment for migraine will be collected upon participants’ enrolment.

*Migraine frequency*. Defined as the number of migraine attacks in four weeks. An attack that is interrupted or rescued by sleep or medications but relapses within 48 hours will be considered as one migraine attack; attacks that are separated by an entire 24-hour period will be considered as two distinct attacks [40]. A 50% reduction in migraine frequency within a evaluation interval will be defined as response.

*Migraine days*. Defined as the number of days with migraine headache within each evaluation interval (four weeks) [41].

*Migraine duration*. Defined as the average duration of each migraine attack.

*Pain intensity*. Evaluated via numeric rating scale (NRS), which is an 11-points scale with 0 indicating no pain and 10 indicating the most severe pain. This outcome will provide data regarding the maximal pain intensity prior to taking abortive medication, as well as the average pain intensity across each observational intervals.

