*Analgesic consumption*. Data collected under this category include the type, amount and frequency of acute medication, participants’ behaviour when purchasing and using analgesics. The quantity of medications will be standardised using medication quantification scales [42], where available.

*Migraine-Specific Quality of Life Questionnaire version 2*.*1 (MSQ)*. A 14-item patient-reporting outcome instrument that measures the impact of migraine on a patient’s health-related quality of life. The domains cover role function-restrictive, role function-preventive and emotional function [43].

*Generalised Anxiety Disorder 7-item (GAD-7) Scale*. An efficient, practical, patient-reporting scale, which is commonly used for rapid screening and evaluating the presence and severity of anxiety disorder, especially in outpatient settings [44].

*Patient Health Questionnaire-9 (PHQ-9)*. A self-administrative scale to screen, diagnose, monitor and measure the severity of depression [45].

*Insomnia Severity Index (ISI)*. A brief self-reporting instrument measuring the patients’ perception of both nocturnal and diurnal symptoms of insomnia [46, 47].

*Satisfaction of treatment*. Evaluated using 5-point Likert scale [48] at each observational timepoint.

*AEs*. Participants will be asked to report any AEs possibly related to prescribed treatments, analgesics or concomitant medications, such as diarrhea, dental ulcer, insomnia in CRFs at observational visits.

During data collection, the researcher will report patients’ scores of GAD-7, PHQ-9 and relevant AEs to the corresponding clinicians to assist in clinical management.

Migraine diary is a tool for patients to record information of migraine attacks and monitor the frequency, duration, severity, associated symptoms and medication consumption of migraine attacks over time. Data collected from migraine diary will be cross-checked with CRFs as a supplementary method to ensure data accuracy.

Clinical records are referred to collect the following information:

*Treatments*, *examinations and diagnoses*. Treatment prescriptions and courses, results of laboratory and medical imaging examinations, Chinese medicine syndrome diagnosis, and western medical diagnoses will be obtained from clinical records.

*Patient-reported MBS*. Any other symptoms such as dry mouth, constipation, abdominal distention, which have been reported by participants, will be extracted from clinical records.

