#### Exposures and confounders

In this real-world observational study, CHM treatment is defined as the main exposure. Participants being treated with CHM solely and those treated with a combination of conventional prophylactic treatment and CHM will be considered as two subcohorts for analyses.

Measured confounders in this study include comorbidities of migraine (depression, anxiety and insomnia, evaluated by PHQ-9, GAD-7, and ISI, respectively), gender, baseline severity of migraine (duration, average frequency, average pain NRS and analgesics consumption at entrance), association with the menstrual cycle (pure menstrual migraine vs menstrually related migraine vs non-menstrual migraine), and aura (migraine with aura vs migraine without aura).

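### Depression, anxiety and insomnia are adjusted for only through symptom scores, so comorbidity already controlled by treatment at baseline can be understated, possibly unequally between the two subcohorts

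*Protocol article*

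**What the plan says.** Under Exposures and confounders, the article names the measured confounders and says how the three psychiatric and sleep comorbidities are assessed: "comorbidities of migraine (depression, anxiety and insomnia, evaluated by PHQ-9, GAD-7, and ISI, respectively"). For these three conditions it names no diagnosis, history or treatment variable. The same section sets up the groups to be analysed: "Participants being treated with CHM solely and those treated with a combination of conventional prophylactic treatment and CHM will be considered as two subcohorts for" […].

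The Introduction lists tricyclic antidepressants, SSRIs and SNRIs among the prophylactic drugs for migraine, and states that "only tricyclic antidepressants, SSNI and SNRI can be adopted for migraine comorbid with depression" (I read the second abbreviation as SSRI). It also says that "the comorbidities in episodic migraine indicate a poor prognosis, leading to poorer quality of life and limiting the response to treatments".

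Under Eligibility criteria, a participant must be seeking migraine treatment at this hospital for the first time. Nothing excludes treatment begun elsewhere or for another indication. The Discussion acknowledges that there is no run-in.

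Under Data collection, "migraine subtypes and other medical histories will be collected upon participant enrolment", and "western medical diagnoses will be obtained from clinical records". Neither item is named as a comorbidity confounder. Under Analytical methods, a disease risk score handles measured confounders and instrumental variables handle unmeasured ones. No instrument is named.

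**The concern.** A symptom score shows how a patient feels now, on whatever treatment the patient is taking. As a confounder, comorbidity matters because it shapes both the choice of treatment and the prognosis, and a patient with controlled depression may still carry part of that.

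The difficulty is the overlap between what lowers the score and what defines the exposure. On the article's own account, the drug classes used when migraine coexists with depression are also conventional prophylactics. A patient who arrives on such a drug and receives CHM may belong to the combination subcohort and have a low PHQ-9 because of that drug. The confounder may then be mismeasured to different degrees in the two groups being compared. The scores could look balanced when the underlying comorbidity is not, and a disease risk score built from them would inherit the error. At stake is any comparison of CHM alone with CHM plus conventional prophylaxis.

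**Working it through.** The article gives no figure to reproduce: no antidepressant use, comorbidity prevalence, scale cut-off or effect size. Every input below is an assumption, and the results only show what size is plausible.

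**Set-up.** Two equal subcohorts with no true difference in response. Depression prevalence is p_B = 0.40 in the combination subcohort and p_A = 0.20 in CHM-only. Depression lowers the response rate by d = 20 points. The score is dichotomised. A share m of depressed patients is masked, meaning they score negative on treatment.

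- Unadjusted confounding: (0.40 − 0.20) × 20 = 4.0 points against the combination subcohort.
- Hidden share among score-negatives in a group: h = p·m / (1 − p(1 − m)).
- Residual bias after adjustment: (h_B − h_A) × d × w, where w is the pooled share scoring negative. The score-positive stratum contributes nothing, because everyone in it is depressed.

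**Masking in the combination subcohort only** (h_A = 0):

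- m = 0: residual 0.
- m = 0.25: h_B = 0.10/0.70 = 0.143; w = (0.70 + 0.80)/2 = 0.75; residual 0.143 × 20 × 0.75 = 2.1 points.
- m = 0.50: h_B = 0.20/0.80 = 0.25; w = (0.80 + 0.80)/2 = 0.80; residual 0.25 × 20 × 0.80 = 4.0 points, so adjustment removes none of the 4.0.

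**The same masking in both subcohorts:**

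- m = 0.25: h_B = 0.143; h_A = 0.05/0.85 = 0.059; w = (0.70 + 0.85)/2 = 0.775; residual 0.084 × 20 × 0.775 = 1.3 points.
- m = 0.50: h_B = 0.25; h_A = 0.10/0.90 = 0.111; w = (0.80 + 0.90)/2 = 0.85; residual 0.139 × 20 × 0.85 = 2.4 points.

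**Half the penalty for controlled patients** (10 points instead of 20, masking in the combination subcohort only): 2.1 becomes 1.1, and 4.0 becomes 2.0.

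**Masking in CHM-only instead** (m = 0.25 there, 0 in combination): h_A = 0.05/0.85 = 0.059; w = (0.60 + 0.85)/2 = 0.725; 0.059 × 20 × 0.725 = 0.9 points, now against CHM-only. The sign depends on where the masked patients sit.

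**A second set of assumptions.** Response is 50% without and 35% with comorbidity. Comorbidity is 30% in CHM-only and 30% to 50% in combination. Masking is 20% to 60% in combination and none in CHM-only. The residual runs from 0.9 to 4.2 points against the combination subcohort. With 30% comorbidity in both groups there is no unadjusted confounding, yet score adjustment creates a bias. At 40% masking, h_B = 0.12/0.82 = 0.146, w = (0.70 + 0.82)/2 = 0.76, and 0.146 × 15 × 0.76 = 1.7 points. With 40% masking in both groups the bias is 0 at equal prevalence and 1.6 points at 30% against 50%.

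**The case against.** The strongest reply is that most of the size comes from choices the article does not make, and much of that reply stands.

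- **No cut-off is stated.** A reader might infer that treated comorbidity is counted as absent. The article gives no yes/no coding and describes PHQ-9 and GAD-7 as measuring severity. With continuous scores, treated comorbidity is understated rather than erased, and the dichotomised figures overstate the effect.
- **The direction is not fixed.** A reader might infer that the error falls mainly on the combination subcohort. That is a structural inference from the Introduction's general list of drugs; nothing describes antidepressant use in this cohort. A drug started at the first visit cannot have lowered the baseline score. The article also does not say whether an antidepressant taken for mood counts as conventional prophylaxis. If it does not, the masked patient may sit in CHM-only.
- **Objective 3.** A reader might infer that the same rule misplaces patients in the analysis of treatment patterns for comorbidities. No section defines those groups by scale score, and the recorded western diagnoses could serve there.
- **Current symptom burden is a defensible adjustment variable.** The Introduction does not say that controlled comorbidity limits response as much as active comorbidity does.
- **The list is open and the article is condensed.** The confounders are introduced as inclusive, instrumental variables are foreseen, and the Discussion urges caution about confounding. This limits the weight of the point but does not dispose of it. The way these three confounders are measured is stated rather than deferred, and an unnamed instrument is a poor substitute for a variable that can be measured from planned data.

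**Conclusion.** The point holds in a limited form. Measuring the three comorbidities by symptom score alone can understate comorbidity that is under control at baseline. The overlap between antidepressants and conventional prophylaxis means the understatement may differ between subcohorts, possibly more in the combination group. The residual confounding is of unknown size. About 1 to 4 percentage points of response rate is what the assumed figures give with a dichotomised score. Equal masking in both groups, a weaker effect of controlled comorbidity, or continuous scores would reduce it, and masking in CHM-only would reverse its sign. The documents do not support saying that treated comorbidity counts as absent, that the error is known to fall mainly on one subcohort, or that Objective 3 is affected. This is a worthwhile and inexpensive correction to the confounder definition. It does not invalidate the design.

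**What to change.** In Exposures and confounders, define each of the three comorbidity confounders by two baseline items: the T0 scale score, and a yes/no covariate for a recorded diagnosis or history of that condition, taken from the enrolment medical history and the western diagnoses in the clinical records. Enter both in the disease risk score, the GEE models and the multivariable regressions. Naming T0 also settles the timing of the scores, since that section ties only migraine severity to entry.

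Do not build current antidepressant treatment into the yes/no covariate. Such a drug can be what places a patient in the combination subcohort, so adjusting for it could remove part of the contrast being estimated. The article also does not show that psychotropic drugs prescribed elsewhere are captured at T0.

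The cost is a sentence or two of text and up to three extra covariates, with no new patients or data items. The benefit depends on how completely histories and diagnoses are recorded. A masked patient with no recorded history stays hidden.

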### Data management

#### Data quality control

Random data check will be conducted during data extraction and data entry to alert on erroneous, missing or out-of-range values and logical inconsistencies. Prompt verification and remedial action will be carried out, where necessary.

#### Data storage and process

The original CRFs will be stored in a locked cabinet for at least five years after the completion of the study. All data will be entered into a Microsoft Excel dataset. Electronic dataset will be stored in a password-protected computer drive. Only the research team members and the ethics committee members will have access to the data.

#### Analytical methods

Data analysis will be conducted in relation to the study objectives:

To summarise participants’ demographic characteristics, preferences and concerns, descriptive analyses will be conducted. Such descriptive analyses will be conducted in subcohorts of patients with various levels of predefined exposures, and compared analysis will be conducted, if appropriate. Categorical variables, including gender and satisfaction degree, will be presented using frequencies and percentages; quantitative variables such as disease duration and migraine frequency will be described with mean values and standard deviation.To display the utilisation pattern of CHM for migraine and to summarise patient-reported MBS, cluster analyses and machine learning algorithms such as Apriori Algorithm [50] will be performed. Apriori Algorithm is a common method to identify core herb pairs and herb combinations [51–53]. Multiple correlation analysis and multivariable regression analysis will be conducted to explore factors related to clinical outcomes, where possible.To evaluate the effects of CHM for adult migraine, generalised estimated equation will be adopted to compare longitudinal differences of clinical outcomes. Disease risk score and instrumental variables will be introduced to control measured and unmeasured confounders, respectively. Missing data will be handled using R-MICE package for the quantitative outcome measures at each evaluation timepoint.

### Ethics considerations

Participants may experience minimal discomfort and inconvenience during the observation. The researcher will communicate with participants professionally to minimise any discomfort associated with their participation in the study. The researcher will also provide detailed answers to any questions raised by the participants related to their migraine and treatments throughout the study. No extra financial, physical nor social demand are anticipated in this study; no payments will be provided to participants. Risk of data leaks is prevented by the well-established data storage and management plan as approved by the Ethics Committee.

Though participants will not receive financial benefits for their participation in this study, they will get a comprehensive assessment of migraine and comorbidities, as well as a monthly summary of and report on their migraine condition. It is expected that the findings of this study will provide pragmatic evidence for future clinical practice for migraine in a real-world setting.

## Discussion

Evidence-based practice has been increasingly used in healthcare [54]. It expects shared clinical decision making that integrates the best available, current, valid and relevant evidence [55]. This real-world observational study will take into consideration of the three vital elements [56] of evidence-based practice [55], namely, CHM utilisation patterns derived from clinical experts’ experience, patients’ preferences and concerns, and current clinical evidence. Other relevant findings such as patients’ quality of life, medication consumptions, sleep disturbances, will also be documented in this study. Hence, this study will provide comprehensive evidence of CHM for migraine in the context of evidence-based practice.

Although RCT evidence is the gold standard to assess the efficacy and safety of CHM, RCT data commonly has poor external validity, thus with limited generalisability in real-world practice. In addition to current RCT findings, this study will provide an extension of evidence from registry studies in clinical practice [36]. To fully capture the benefits of individualised interventions, patient-reported outcomes are recommended to be included along with standardised outcome measures [36]. Compared with RCT evidence, this real-world study may involve a broad range of participants, including chronic migraine with medication overuse, and migraine with psychiatric comorbidities. Findings from this study will fill in data gaps of the effects of CHM for these subtypes of migraine patients. In addition, this observational study innovatively applies patient-reported MBS in addition to common migraine outcomes to provide more comprehensive clinical assessments.

Previously, Chinese medicine practitioners’ experience of using CHM for migraine were reported in retrospective studies based on clinical records and published data [57–61]. It should be noted that, retrospective studies often introduce bias or confounding factors which may impact on the interpretation of their results [62]. Unlike previous studies, this prospective study will provide more reliable and relevant data based on structured outcome measures and regular data collection throughout the observational period.

Common limitations of registry-based cohort studies and real-world studies are inevitable and cannot be completely excluded in this research. These include the lack of run-in period and randomisation, the subsequent recall bias [63] and various confounders [64]. Disease risk score and instrumental variables could be applied to deal with the confounders, and caution should be paid during the interpretation of these findings. Finally, this study is designed as a single-centre cohort, and the geographic limitation should be noted.

